## STUDY SYNOPSIS

|                                      |                                                                                                                                                                                                                                                                                                                                                                                                                                                                                                                                                                                                                                                                                                                                                                                                                                                                                                                                                                                                                                                                                                                                                                                                                                                                                                                                                                                                                                                                                                                                                                                                                                     |
|--------------------------------------|-------------------------------------------------------------------------------------------------------------------------------------------------------------------------------------------------------------------------------------------------------------------------------------------------------------------------------------------------------------------------------------------------------------------------------------------------------------------------------------------------------------------------------------------------------------------------------------------------------------------------------------------------------------------------------------------------------------------------------------------------------------------------------------------------------------------------------------------------------------------------------------------------------------------------------------------------------------------------------------------------------------------------------------------------------------------------------------------------------------------------------------------------------------------------------------------------------------------------------------------------------------------------------------------------------------------------------------------------------------------------------------------------------------------------------------------------------------------------------------------------------------------------------------------------------------------------------------------------------------------------------------|

| Study Title:                  | Improving Inappropriate Medication and Information Transfer at Hospital Discharge.
A Cluster-RCT                                                                                                                                                                                                                                                                                                                                                                                                                                                                                                                                                                                                                                                                                                                                                                                                                                                                                                                                                                                                                                                                                                                                                                                                                                                                                                                                                                                                                                                                                                                                 |
| Short Title/Study ID:         | HDS – The Hospital Discharge Study                                                                                                                                                                                                                                                                                                                                                                                                                                                                                                                                                                                                                                                                                                                                                                                                                                                                                                                                                                                                                                                                                                                                                                                                                                                                                                                                                                                                                                                                                                                                                                                                  |
| Protocol Version and Date:    | Version 1.1 of March 07, 2018                                                                                                                                                                                                                                                                                                                                                                                                                                                                                                                                                                                                                                                                                                                                                                                                                                                                                                                                                                                                                                                                                                                                                                                                                                                                                                                                                                                                                                                                                                                                                                                                       |
| Trial registration:           | Study registry: ISRCTN
Registration number: ISRCTN18427377                                                                                                                                                                                                                                                                                                                                                                                                                                                                                                                                                                                                                                                                                                                                                                                                                                                                                                                                                                                                                                                                                                                                                                                                                                                                                                                                                                                                                                                                                                                                                                       |
| Study category and Rationale: | Other clinical study, category A

The intervention will comprise aspects of communication as well as critical reviews and optimizations of discharge medication plans with the possibility to immediately reverse any change in case of unintended side-effects.                                                                                                                                                                                                                                                                                                                                                                                                                                                                                                                                                                                                                                                                                                                                                                                                                                                                                                                                                                                                                                                                                                                                                                                                                                                                                                                                                              |
| Background and Rationale:     | 
Inappropriate medication and polypharmacy increase morbidity, hospitalization rate, costs and mortality in multimorbid patients. At discharge from hospital, polypharmacy is substantially increased compared to admission. Although interventions to reduce polypharmacy exist in variable grades of complexity and dissemination, up to now their use has been rather restricted to specialized settings like geriatric medicine or pharmacology but not widely adopted at the crucial interface between hospital physicians (HPs) and general practitioners (GPs).
 
Moreover, optimally reduced medication plans at hospital discharge do not suffice to achieve sustained polypharmacy reduction. Switching back to the pre-hospitalization medication scheme is known to be a common pitfall to be avoided on the way to reduce polypharmacy. Therefore, a consensus between HPs and referring GPs with regard to the discharge medication plans, resulting from the involvement of the latter in the prescription/deprescription decisions at hospital discharge, is a suitable measure to increase adoption rates of optimized discharge medication plans.
 
The present trial falls in line with other recent studies which showed that planned discharge interventions can considerably reduce re-hospitalization rates and extend time to readmission. To our knowledge, it will be the first study to analyze the combination of a brief deprescribing intervention with a standardized communication strategy between HPs and GPs, at discharge from hospital and in the early post-discharge period.
 |

|                                      |                                                                                                                                                                                                                                                                                                                                                                                                                                                                                                                                                                                                                                                                                                                                                                                                                                                                                                                                                                                                                                                                                                                                                                         |
|--------------------------------------|-------------------------------------------------------------------------------------------------------------------------------------------------------------------------------------------------------------------------------------------------------------------------------------------------------------------------------------------------------------------------------------------------------------------------------------------------------------------------------------------------------------------------------------------------------------------------------------------------------------------------------------------------------------------------------------------------------------------------------------------------------------------------------------------------------------------------------------------------------------------------------------------------------------------------------------------------------------------------------------------------------------------------------------------------------------------------------------------------------------------------------------------------------------------------|
| Objectives:                   | 
To test the hypothesis that a simple medication review tool in combination with a defined communication strategy at hospital discharge leads to prolonged hospital re-admission times compared to usual care (control group), and has the potential to improve patients' health outcomes.
 
To identify best practice of how to implement this approach in daily routine at hospital discharge.
 
To estimate the potential cost savings of this approach.
 
To foster dissemination of this approach (if successful) among Swiss hospital wards and GPs.
                                                                                                                                                                                                                                                                                                                                                                                                                                                                                                                                                                                         |
| Outcomes:                     | 
Primary outcome:
 
 
• Time (days) without readmission to hospital, within 6 months
 
 
Secondary outcomes:
 
 
• Hospital readmission rates within 1, 3 and 6 months
 
• Number of emergency department (ED) visits within 1, 3 and 6 months
 
• Number of GP encounters within 1, 3 and 6 months
 
• Death during follow-up of 6 months
 
• Differences in the number of drugs per patient at discharge, 1, 3 and 6 months, between intervention and control group.
 
• Anatomical therapeutic chemical classes (ATC codes) of the drugs prescribed/de-prescribed
 
• Proportion of potentially inappropriate medications (PIMs) at discharge, 1, 3 and 6 months
 
• Patients' quality of life at discharge, 1, 3 and 6 months
 
• Frequency of utilization of the communication offer (phone calls of GPs to HPs)
 
• Ratings of feasibility/acceptance by HPs
 
• Barriers and enablers of deprescribing among HPs and among patients
 
• Dropout rates of HPs, GPs and patients
 
 |
| Study Design:                 | Single-center double-blind cluster-randomized parallel-controlled clinical trial with a 6-month follow up.                                                                                                                                                                                                                                                                                                                                                                                                                                                                                                                                                                                                                                                                                                                                                                                                                                                                                                                                                                                                                                                              |
| Inclusion/Exclusion Criteria: | 
Inclusion criteria: In-hospital patients will be eligible if they are 60 years or older and prescribed 5 or more drugs.
 
Exclusion criteria: Cognitive inability to follow study procedures or end-stage disease with a life expectancy of less than 3 months.
                                                                                                                                                                                                                                                                                                                                                                                                                                                                                                                                                                                                                                                                                                                                                                                                                                                                                             |

|                                               |                                                                                                                                                                                                                                                                                                                                                                                                                                                                                                                                                                                                                                                                                                                                                                                                                                                                                                                |
|-----------------------------------------------|----------------------------------------------------------------------------------------------------------------------------------------------------------------------------------------------------------------------------------------------------------------------------------------------------------------------------------------------------------------------------------------------------------------------------------------------------------------------------------------------------------------------------------------------------------------------------------------------------------------------------------------------------------------------------------------------------------------------------------------------------------------------------------------------------------------------------------------------------------------------------------------------------------------|
| Study Intervention:                    | 
1: A “teach-the teacher” training session for the senior HPs in charge of postgraduate education and supervision of the interns (assistant physicians). The purpose of this training of 2 hours duration is to integrate the discharge procedure (see below) into the daily work of the intern HPs during the study period. Consecutively, the senior HPs will teach the interns how to apply the structured discharge procedure. This will assure the consistency of the intervention, as the fluctuation among interns is high due to job rotations within hospitals.
 
2: The intern HP performs a critical review of the medication plan, supervised by his senior HP, discusses the results of this review and his suggestions with the patient, and creates a medication plan.
 
3: This revised medication plan is communicated to the patient’s GP with an invitation for discussion.
 |
| Reference Intervention:                | The HPs in the control group will undergo a 2-hour educative session addressing multimorbidity, patient in- and exclusion and the handling of the different data collection forms.                                                                                                                                                                                                                                                                                                                                                                                                                                                                                                                                                                                                                                                                                                                             |
| Number of Participants with Rationale: | 
Based on published readmission rates, an exponential survival curve has been modeled. We defined a delay in time to readmission of 25% as relevant. This translates into a difference in medians of 23 days (from 93 to 116 days) and corresponds to a hazard ratio of 0.80 between intervention and control group participants. We assumed a two-sided alpha of 0.05, a power of 80%, an intraclass correlation coefficient (ICC) of 0.02, an overall censoring probability of 40%, and a cluster size of 50 patients per senior HP. Thus, 21 senior HPs and 1’050 patients per arm are needed, i.e. 42 senior HPs and 2’100 patients in total.
 
An interim analysis with 50% of the full sample size is planned in case of poor recruitment success.
                                                                                                                                            |
| Study Duration:                        | Patients will be recruited during 4 months or until the designated number of patients per cluster is reached, and follow up will last for 6 months for each patient.                                                                                                                                                                                                                                                                                                                                                                                                                                                                                                                                                                                                                                                                                                                                           |
| Study Schedule:                        | Pilot test, first participant in (planned): 03/2018
RCT, last participant out (planned): 03/2019                                                                                                                                                                                                                                                                                                                                                                                                                                                                                                                                                                                                                                                                                                                                                                                                            |

|                                    |                                                                                                                                                                                                                                                                                                                                                                                                                                                                                                                                                                                                                                                                                                                                                                                                                                                                                                                                                                                                                                                                                                                                                                                                                                                                                       |

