#### *b. The hospital discharge issue*

Readmission after hospital discharge is a frequent event: In the US, one in 5 hospitalized Medicare beneficiaries is readmitted within 30 days, at a cost of more than \$ 26 billion per year (19). In the recent years 2011 and 2012, these rates were quite stable, at 19% and 18.4%, respectively (12). In a German health assurance claims sample from 2003, the 30-day readmission rate among a sample of nearly 200'000 patients was very similar with 18.5% (47). Own (not published) data of the UniversityHospital of Zurich show a similar 30-day readmission rate of 17% and a 90-day readmission rate of 27% for multimorbid elderly patients ( $\geq 60$  years).

Studies using different discharge interventions show effects between 15% and 50% readmission rate reduction, mainly at the 30-day post-discharge time point (28, 48). A recent systematic review from the Cochrane Collaboration (13) demonstrated an average 13% relative risk reduction for readmissions by planned discharge interventions (RR 0.87; 95% CI 0.79-0.97) from 15 trials, and time to readmission could be extended by half (from 12 to 18 days) in a frail population of older adults ( $\geq 60$  years) by a transitional care program (46). Costantino et al. found that the earlier a multifaceted intervention took place after discharge from hospital the greater was the reduction in the readmission rate (7).

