### 11.2 Determination of Sample Size

We modeled hospital readmission time by fitting an exponential survival curve on published readmission rates (48, 46) and internal data from the University Hospital Zurich. Extending readmission time by 25% was considered a relevant effect of the intervention. In the fitted model, this translates into an increase of the median readmission time by 23.2 days (from 92.7 days to 116.8 days) and corresponds to a hazard ratio of 0.80 between intervention and control group participants. This is equivalent to a decrease of 18.2% in readmission rates after 30 days (from 20.1% to 16.4%).

Based on this hazard ratio and assuming a two-sided  $\alpha = 5\%$ , a power of  $1 - \beta = 80\%$ , an intraclass correlation coefficient (ICC) of 0.02 as in (18), 40% overall censoring probability and equally sized clusters of 50 patients, we calculated a sample size of 21 clusters and 1'050 individuals per trial arm. Thus, 42 senior HPs and 2'100 patients in total will need to be included in order to observe a relevant effect of the study intervention with sufficient power.

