#### 11.3.2 Primary Analysis

Descriptive statistical methods will be used to describe the study population, including dropouts and losses to follow up. Baseline characteristics of the intervention and control groups will be calculated with corresponding 95% confidence intervals where applicable.

The primary outcome will be compared between groups using Kaplan-Meier and log rank tests. To compare factors which may affect readmission, Cox regression (proportional hazards model) will be used considering hospital clinics/units as clusters. The multivariable model will include patient characteristics as factors as well as all covariates used for balanced allocation of clusters to the study arms, and subgroup analyses may be carried out for such factors or covariates.

For secondary outcomes, parametric ( $t$ -test) or non-parametric tests ( $\chi^2$ - and Wilcoxon test) will be used where appropriate.

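### A 25% delay, a 23-day difference in medians and HR 0.80 are the same effect only under a constant hazard, which the protocol's own readmission rates contradict

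*Protocol*

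**What the plan says.** The synopsis (Number of Participants with Rationale) sets the threshold: "We defined a delay in time to readmission of 25% as relevant". It then converts it: "This translates into a difference in medians of 23 days (from 93 to 116 days) and corresponds to a hazard ratio of 0.80". Section 11.2 repeats the criterion, "Extending readmission time by 25% was considered a relevant effect of the intervention", and gives the control median as 92.7 days and the 30-day readmission rates as 20.1% and 16.4%. It says that an exponential curve was fitted to two published sources and to internal data from the University Hospital Zurich.

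The design inputs are in the synopsis: "We assumed a two-sided alpha of 0.05, a power of 80"%, an ICC of 0.02, and "an overall censoring probability of 40%, and a cluster size of 50 patients per senior HP".

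The outcome is limited to the follow-up period: "Time (days) without readmission to hospital, within 6 months". The planned comparison in 11.3.2 is: "The primary outcome will be compared between groups using Kaplan-Meier and log rank tests", with Cox regression for factors that may affect readmission.

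Section 3.3 (hospital discharge issue) reports unpublished data of the same University Hospital for multimorbid patients aged 60 or older: a "30-day readmission rate of 17% and a 90-day readmission rate of 27"%.

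**The concern.** Under a constant hazard, multiplying all readmission times by 1.25 multiplies the median by 1.25 and gives a hazard ratio of 1/1.25 = 0.80. If the hazard falls with time, the three statements separate. A 25% delay then means a hazard ratio closer to 1, and HR 0.80 means a delay longer than 25%. The rates in 3.3 show a falling hazard: a constant risk that gives 17% at 30 days would give 1 - 0.83^3 = 43% at 90 days, not 27%.

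The meaning of the target is at stake. The sponsor calls a 25% delay relevant but powers the trial for HR 0.80. If these are different effects, a result that meets one need not meet the other. The only figure in days that the protocol offers, the 23-day difference in medians, may also be impossible to observe within 6 months.

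**Working it through.** **Inputs.** From the synopsis and 11.2: control median 92.7 days, time ratio 1.25, HR 0.80, two-sided alpha 0.05, power 80%, 40% censored, ICC 0.02, 50 patients per cluster. From 3.3: 17% readmitted at 30 days, 27% at 90 days. Follow-up is 6 months (180 to 182.5 days).

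**1. The plan's own figures.**
- Events for HR 0.80 (Schoenfeld): 631. Divided by 0.60: 1,052. Times the design effect 1 + 49 × 0.02 = 1.98: 2,082, which rounds up to 21 clusters of 50 per arm, or 2,100 patients. The sample size reproduces.
- Exponential rate: ln 2 / 92.7 = 0.00748 per day. At 30 days, 1 - exp(-0.00748 × 30) = 20.1%; with HR 0.80, 16.4%. Both match 11.2.
- Median under a 25% delay: 1.25 × 92.7 = 115.9 days, a gain of 23.2 days, as in the synopsis. (Section 11.2 prints 116.8, which would be a gain of 24.1.)

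**2. The model against section 3.3.**
- Exponential prediction at 90 days: 1 - exp(-0.00748 × 90) = 49.0%, against 27% reported.
- Cumulative hazards from 3.3: H(30) = -ln 0.83 = 0.186; H(90) = -ln 0.73 = 0.315.
- Daily hazard, days 0 to 30: 0.186/30 = 0.0062. Days 30 to 90: (0.315 - 0.186)/60 = 0.0021, about one third.

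**3. Two curves through both reported points.**
- Weibull: shape = ln(0.315/0.186)/ln 3 = 0.477. About 36% are readmitted by 6 months; the control median is about 471 days.
- Piecewise constant hazard with a change at day 30: about 40% by 6 months; the control median is about 267 days.
- For the control median to fall at day 180, the hazard after day 90 would have to be (0.693 - 0.315)/90 = 0.0042 per day, double that of days 30 to 90.

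**4. What a 25% delay means on these curves.**
- Weibull: HR = 1.25^(-0.477) = 0.90 (0.889 to 0.909 over the rounding of the two rates). Conversely, HR 0.80 is a time ratio of 0.8^(-1/0.477) = 1.60, a delay of about 60%.
- Piecewise: the hazards are not proportional under a stretch of time. A Cox fit to a large simulated sample, censored at 180 days, gives an average HR of 0.85.

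**5. What HR 0.80 means in days within follow-up.** Mean readmission-free time to day 182.5 is the area under the survival curve.

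| Curve | Control | HR 0.80 | Gain (days) |
|---|---|---|---|
| Exponential, median 92.7 | 99.6 | 111.1 | 11.5 |
| Weibull | 136.1 | 144.2 | 8.1 |
| Piecewise | 135.4 | 143.5 | 8.1 |

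**The case against.** **The assumption is disclosed.** The synopsis says that an exponential curve was modelled, and 11.2 speaks of the fitted model. This is true. But disclosing the assumption does not remove the conflict with the 90-day rate in 3.3, which comes from the hospital whose internal data are said to have entered the fit.

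**The contrary evidence is thin.** The 27% is one hospital's unpublished figure, the trial recruits in many hospitals and requires five or more drugs, and 6-month values extrapolate from day 90. The two published sources behind the curve are not reproduced in the protocol. A least-squares exponential through the two points has a median near 178 days, just inside follow-up. This stands as a limit on certainty. That exponential fits badly, however: it gives 11% at 30 days and 30% at 90 days. The documents offer no other 90-day figure.

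**The primary test needs no median.** This stands in full. A reader might infer that the trial cannot show whether its threshold is met. The documents do not support that: log rank and Cox do not use the median, an estimated HR can be set against 0.80, and a delay can be read from an earlier quantile (under the Weibull, the 25th percentile moves from about 75 to 93 days).

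**The discrepancy depends on how many events occur.** This also stands. A reader might infer that it would persist unchanged with all 1,260 planned events (60% of 2,100). But 60% readmitted within 6 months implies a different curve and an overall median that is reached. A Weibull through 17% at day 30 and 60% at day 180 has shape 0.89. A 25% delay is then HR 0.82, with about 71% power on 1,260 events. Combining the HR from a curve with about 36% readmitted with 60% events would describe no coherent scenario.

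**Conclusion.** The equivalence is wrong as written when judged by the protocol's own figures. The constant hazard that it needs predicts 49% readmitted at 90 days where 3.3 reports 27%. On the two curves that fit both rates in 3.3, a 25% delay is an HR of about 0.85 to 0.90, so the 80% power stated for HR 0.80 does not apply to the effect called relevant. The medians of 93 and 116 days are unlikely to be observed, with about 36% to 40% of controls readmitted by 6 months.

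The range of HRs depends on the form of curve, and the 6-month percentages assume that the hazard does not rise after day 90 and that the single source resembles the trial population. The conflict at day 90 needs neither assumption.

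The sample size for HR 0.80 follows from its stated inputs, and the primary test is not invalidated. Nor should a gain of 11.5 restricted-mean days be read as showing that the 23 days are twice too large: one is a mean cut at 6 months, the other a difference in medians. The protocol should give the first because it matches the outcome as worded and can be estimated within follow-up.

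**What to change.** - **Synopsis and 11.2:** state the target effect as HR 0.80. Delete the equivalence with a 25% delay and a 23-day difference in medians, or say that it holds only under a constant hazard that the rates in 3.3 do not support. Give instead the gain in mean readmission-free days to 6 months that HR 0.80 implies: about 8 days on the figures in 3.3 and 11.5 in the exponential model.
- **11.3.2:** add, as a supportive estimate in days, the difference between arms in restricted mean readmission-free time to 6 months, with a cluster-robust confidence interval (for example pseudo-observations in a GEE with the clinic or ward as cluster). Report medians only if they are reached.

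The cost is wording in two places and one extra analysis of data already collected. This change needs no more patients. The quoted effect in days becomes less favourable.
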